#### Access to Usual Care

All participants in the study, including those in the BI and BIM groups, will continue to have access to usual care throughout the study period. Usual care refers to the standard clinical management offered by primary care physicians and nurses, which may include dietary advice, physical activity counseling, laxative prescriptions, or follow-up visits, depending on individual needs and clinical judgment. No restrictions are placed on access to routine health care.

### Ethical Considerations

The study was designed in accordance with the principles of the World Medical Association Declaration of Helsinki, as amended in 2013, and applicable regulations. The protocol was approved by the ethics committee of Jordi Gol Primary Care Research Institute (Barcelona, January 22, 2024; code 23/253-P).

The data controller and processor will be the Catalan Institute of Health. The database will be stored for a period of 10 years. The data obtained will not be disclosed to third parties by the research team. International transfers are not provided for. Security mechanisms are sufficient to prevent breaches of confidentiality.

Participants will be informed of the objectives and general aspects of this study and will be asked for informed consent. The informed consent form will specifically include the voluntary nature of participation, security measures, and the confidentiality of the data and its exclusive use for research purposes.

The European Data Protection Regulation 2016/679 of the European Parliament and of the Council of 27 April 2016 on the protection of natural persons with regard to the processing of personal data and the free movement of such data and the Organic Law 3/2018 of 5 December on the Protection of Personal Data and guarantee of digital rights will be complied with at all times.

This protocol has been registered on ClinicalTrials.gov (NCT06359249). The final results will be submitted for publication in peer-reviewed journals and presented at relevant national and international conferences. In addition, findings will be shared with participating primary care centers and regional health authorities to support possible adoption into clinical practice. Participants will be informed of the study results through summary reports distributed via their primary care teams.

## Results

### Progress

Participant enrollment concluded in August 2025, and data collection is ongoing and expected to continue until April 2026. The primary and secondary outcomes will be assessed at 3, 6, and 12 months after the intervention. Results will be analyzed using RStudio and reported in accordance with the Consolidated Standards Of Reporting Trials (CONSORT) guidelines for randomized trials.

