The primary objective of this study is to evaluate the effectiveness of a structured rehabilitation program based on behavioral reeducation and abdominal massage therapy in reducing the prevalence of chronic constipation and the use of laxatives at 3, 6, and 12 months after the intervention. The secondary objectives are to assess changes in quality of life among participants and to evaluate whether the observed effects are sustained over time.

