### Design: Randomized Controlled Trial

This will be a randomized controlled trial with 3 groups: a control group, a behavioral intervention (BI) group, and a behavioral intervention and massage (BIM) group. The same number of people will be randomly distributed in each group with a 1:1:1 allocation ratio, so that the 3 groups are homogeneous for age, sex, and constipation characteristics. Data collection will be between 2024 and 2026.

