### Intervention

#### BI Group

The behavioral education sessions are structured into two 60-minute workshops delivered in a progressive format. Session 1 focuses on understanding the physiology of defecation, the Rome IV diagnostic criteria, and bowel habits. Session 2 addresses lifestyle-related components, including dietary fiber and hydration guidelines, physical activity recommendations, stress management, optimal defecation posture, and the rational use of laxatives. The sessions are delivered by a multidisciplinary team (nurse, physician, physiotherapist, nutritionist, and psychologist) using multimedia presentations and printed handouts. Participants are encouraged to set personal bowel health goals. Questions and doubts raised during the first session will be discussed and resolved in the second session, ensuring continuity of learning and participant engagement.

The Bristol scale, Rome IV criteria, CVE-20 quality of life questionnaire, and International Physical Activity Questionnaire (IPAQ) [11,29-31] will be explained, and a calendar will be given to the patients to mark when they take any laxatives. Once the information sessions are complete, follow-ups will be scheduled 3 and 6 months later.

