#### BIM Group

The BIM group will receive the same intervention as the BI group, and the group will also participate in two 30-minute sessions with the physiotherapist to learn how to perform abdominal massage. In these sessions, the technique will be explained and an explanatory leaflet will be given to the participants so that they can do the massage independently at home.

The abdominal massage protocol follows a standardized clockwise technique that mirrors the path of the colon. The massage begins in the right lower quadrant (ascending colon), progresses to the upper abdomen (transverse colon), and concludes in the left lower quadrant (descending colon). Techniques include gentle effleurage, deep circular kneading, and vibration movements, applied in a slow, consistent rhythm. Each session lasts approximately 30 minutes. Participants are instructed to perform the massage once daily, preferably 20 to 30 minutes after a main meal, in a supine position with knees slightly flexed. The physiotherapist demonstrates the technique and provides a printed visual guide for home practice. The therapist will verify that participants have correctly learned the abdominal massage technique and are able to perform it independently.

To support adherence to the abdominal massage protocol, participants will be provided with a daily self-recording calendar to note each time they perform the massage at home. This calendar will be reviewed at follow-up visits. In addition, weekly SMS reminders will be sent to participants in the BIM group, encouraging them to maintain the daily routine and reinforcing key points of the technique.

Once these sessions are finished, follow-up sessions will be scheduled at 3 and 6 months. Participants will complete the questionnaires again and return the calendar, with marks showing when laxatives were used and massages performed.

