#### Control Group

The control group will receive the usual care in their primary care center and will be asked to complete the Bristol scale, Rome IV criteria, CVE-20 quality of life questionnaire, and IPAQ [11,29,30] at the beginning of the study and after 3, 6, and 12 months. They will also be given the calendar to mark when they take laxatives. This calendar will be collected after 3 months.

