### Future Directions

Should the findings be favorable, future research should focus on scaling the intervention to other regions and health care systems, increasing the sample size, and assessing long-term outcomes, beyond 6 months. Moreover, future studies could include a sham massage group to control for attention bias and better isolate the effect of abdominal massage.

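### The 12-month outcome in the primary objective cannot be complete for all randomised participants by April 2026, and the arm schedules disagree on whether all three arms are seen at 12 months

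*Protocol article*

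**What the plan says.** The article gives two different follow-up horizons.

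**Twelve months included**
- The primary objective, at the end of the Introduction, covers constipation and "the use of laxatives at 3, 6, and 12 months after the intervention".
- Progress: "The primary and secondary outcomes will be assessed at 3, 6, and 12 months after the intervention".
- Variables and Table 1 list T12 for the Rome IV criteria, Bristol scale, CVE-20, IPAQ and laxative calendar, with no restriction to an arm.
- Control Group: questionnaires "at the beginning of the study and after 3, 6, and 12 months".

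**Three and six months only**
- BI Group: "Once the information sessions are complete, follow-ups will be scheduled 3 and 6 months later".
- BIM Group: "Once these sessions are finished, follow-up sessions will be scheduled at 3 and 6 months".
- The Abstract, the main variable in Statistical Analysis and the anticipated findings in the Discussion all use 3 and 6 months.
- Future Directions lists "assessing long-term outcomes, beyond 6 months" among the tasks for later research.

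**Calendar**
- Progress: "Participant enrollment concluded in August 2025, and data collection is ongoing and expected to continue until April 2026".
- Design gives only a broad window: "Data collection will be between 2024 and 2026".

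**The concern.** The primary objective names a time point that the stated dates cannot deliver for everyone randomised, and the sections describing each arm do not schedule it alike.

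Two things are at stake. First, Statistical Analysis promises intention to treat with all randomised participants. At month 12 that set could not be fully observed under the stated dates, and whether a participant is observed would depend on enrolment date. If the arm descriptions were followed literally, it would also depend on arm. Second, with the horizon unsettled, the trial's conclusion on its primary objective could be drawn at 6 or at 12 months, and nothing in the article fixes which. That choice should be made before results are seen.

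**Working it through.** **Inputs from the article.** Enrolment closed in August 2025 and collection is expected to end in April 2026 (Progress). Ethics approval was on 22 January 2024 (Ethical Considerations), taken here as the earliest possible start. There are 45 participants, 15 per group (Sample and Randomization). The month enrolment began and the delay from enrolment to the end of the sessions are not given.

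**Step 1. Time available after the last enrolment.** Days divided by 30.4375:
- 1 August 2025 to 30 April 2026: 272 days = 8.9 months (longest).
- 31 August 2025 to 1 April 2026: 213 days = 7.0 months (shortest).
- Same day in each month: 8 months.

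**Step 2. Does the 6-month visit fit?** August 2025 + 6 months = February 2026, before April 2026. Counting back, 30 April 2026 − 6 months = end of October 2025. The 6-month visit therefore fits for the last enrolees if their sessions were finished by about then.

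**Step 3. Does the 12-month visit fit?** August 2025 + 12 months = August 2026. That is 4 months after April 2026 (3 to 5 depending on the days). Counting back, April 2026 − 12 months = April 2025, so only participants whose intervention ended by about April 2025 can be observed at month 12.

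**Step 4. How many could reach month 12?** This needs an assumption. Take uniform accrual from a start date *s* to 31 August 2025, month 12 counted from enrolment, and collection until 30 April 2026:

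share = (30 April 2025 − *s*) / (31 August 2025 − *s*)

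| Assumed start *s* | Days | Share | Of 45 |
|---|---|---|---|
| 22 January 2024 | 464 / 587 | 79% | 35.6 |
| 1 July 2024 | 303 / 426 | 71% | 32.0 |
| 1 January 2025 | 119 / 242 | 49% | 22.1 |
| 1 April 2025 | 29 / 152 | 19% | 8.6 |
| 1 May 2025 | none before the cut-off | 0% | 0 |

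Counting from enrolment favours the plan. The objective counts from the intervention, so any delay until the sessions end lowers these shares.

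**Step 5. Arm schedules side by side.**

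| Source | BI | BIM | Control |
|---|---|---|---|
| Arm descriptions | 3, 6 | 3, 6 | 3, 6, 12 |
| Progress, Variables, Table 1 | 3, 6, 12 | 3, 6, 12 | 3, 6, 12 |
| Main variable (Statistical Analysis) | 3, 6 | 3, 6 | 3, 6 |

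No two rows agree. The laxative calendar shows the same strain: Table 1 lists it at T3, T6 and T12, while Control Group has it collected after 3 months.

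**The case against.** The strongest reply is that the article does not rule out month 12.

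- **A reader might infer that the 12-month outcome is unobtainable.** The documents do not support that. Early participants can reach month 12 before April 2026, and on the most favourable start date considered they are the majority. The April 2026 date is also a forecast, and the broad window in Design, which runs into 2026, leaves room for an August 2026 visit. What stands is that completeness for all randomised participants is incompatible with the specific end date in Progress.
- **A reader might infer that none of the roughly 30 BI and BIM participants has a 12-month visit, so that no randomised comparison exists.** That takes one side of a contradiction as the answer. Progress, Variables and Table 1 list month 12 without limiting it to an arm, and the BI and BIM descriptions do not say that follow-up stops at 6 months. What stands is that the sections conflict.
- **A reader might infer that unobserved 12-month values will be imputed for people never due a visit.** Statistical Analysis states multiple imputation under missing at random, but names no 12-month analysis. The handling of visits lost to the closing date may sit in an analysis plan that is not shown. This is a risk to close off, not something the article says.
- **A reader might take April 2026 as proof that only 6 months was ever intended.** That match needs about 2 months for sessions after the last enrolment, a figure the article does not give.

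It is also fair to say that the sample size rests on 3 months and the main variable on 3 and 6 months, so the core comparison does not depend on month 12.

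**Conclusion.** The point holds as an internal inconsistency in the primary objective. Under the dates in Progress, 12-month data cannot be complete for all randomised participants. The gap for the last enrolees is about 4 months (3 to 5), and the cut-off falls at an intervention ending in about April 2025. This rests only on the stated dates.

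The number affected is not known. The range of 79% to 0% able to reach month 12 rests on assumed uniform accrual, an assumed start date and no delay before the sessions end. Separately, the arm descriptions, the general schedule and the definition of the main variable give three different follow-up patterns.

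The damage is confined to the 12-month part of the objective. The 3- and 6-month comparisons are not affected by the point.

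**What to change.** Reconcile the primary objective, Design, Control Group, Progress, Variables and Table 1 with the Abstract, BI Group, BIM Group, Statistical Analysis and the anticipated findings. Do it by a dated and justified amendment before analysis, choosing one of two routes.

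**(a) Conclude on 3 and 6 months.** Limit the primary objective and its conclusions to those time points. Report any 12-month data already collected descriptively, with numbers by arm, and do not impute month 12 for participants who could not reach it or were not scheduled for it. *Cost:* no new data, but the confirmatory 12-month claim is given up. Dropping a prespecified time point after enrolment has closed is a substantive change and must be recorded as such.

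**(b) Keep 12 months.** Schedule it identically in all three arms, including the laxative calendar, and extend collection to the last participant's 12-month visit, at least about 4 months beyond April 2026. August 2026 lies within the window given in Design if the sessions followed enrolment promptly. *Cost:* one more questionnaire round for at most 45 people and a later end date.

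Route (b) gets harder once collection closes, so the choice should not wait. Under either route, state when enrolment began and how many participants in each arm can reach month 12.

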### Dissemination Plans

The study’s findings will be disseminated through peer-reviewed publications and presentations at national and international conferences.

### Variables

We will evaluate a set of indicators on constipation and other patient characteristics, as shown in Table 1. Outcomes will be assessed individually and at 5 different time points: before starting the intervention, on the same day of the intervention, 3 months after the intervention, 6 months after the intervention, and 12 months after the intervention. Data will be collected through standardized questionnaires to be completed independently by the participants.

**Table 1. T1:** Study variables.

Study area and instrument		Measurement time point
Constipation		
	Rome IV criteria—degree of constipation	Tpre^a^, T0^b^, T3^c^, T6^d^, T12^e^
	Bristol Stool Form Scale—stool type	T0, T3, T6, T12
Quality of life		
	CVE-20 questionnaire	T0, T3, T6, T12
Use of laxatives		
	Self-recorded calendar of laxative intake	T3, T6, T12
Patient characteristics		
	ECAP^f^—sex, age, previous conditions	Tpre
	IPAQ^g^—physical activity level	T0, T3, T6, T12
Habit change intention		
	Dichotomous question	T0

a Tpre: before the intervention.

b T0: start of the intervention.

c T3: 3 months after the intervention.

d T6: 6 months after the intervention.

e T12: 12 months after the intervention.

f ECAP: Electronic Primary Care Clinical Workstation.

g IPAQ: International Questionnaire of Physical Activity.

### Statistical Analysis

The main variable will be the percentage of patients with constipation 3 and 6 months after the start of treatment for each group, a dichotomous qualitative variable. Prevalence will be estimated and analyzed using the *χ*^2^ test.

The other variables will be reported as percentages and counts for categorical variables and through mean, median, deviation, and quartiles for continuous variables. In order to analyze relationships between the main variable and the sociodemographic or other explanatory variables, the *χ*^2^ test will be used, and the relative risk will be estimated to compare the reduction between the two intervention groups with respect to the control group.

To evaluate the secondary variable, a continuous quantitative variable, ANOVA or the Kruskal-Wallis test will be used to determine differences between the 3 groups. To determine differences between pairs of groups, the Student *t* test or Mann-Whitney test will be used. Analyses will use 95% CIs, and the significance level will be set at 5%.

Due to the nature of the intervention, participant blinding is not feasible. However, to minimize potential bias in outcome assessment, data entry and statistical analysis will be performed by a researcher who is blinded to group allocation. This approach ensures objectivity in the interpretation of results, particularly for subjective outcome measures. All analyses will follow the intention-to-treat principle, including all randomized participants in the groups to which they were originally assigned. Missing data will be handled using multiple imputation under the assumption that data are missing at random. Statistical analysis will be performed with RStudio.

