### Sample and Randomization

Calculations were based on published evidence suggesting that approximately 90% of patients in the control group would remain constipated at 3 months. We hypothesized that this proportion would decrease to 40% in the intervention groups (BI and BIM), corresponding to a 50% absolute difference. To detect this difference with 80% power and a 2-sided significance level of 5%, while allowing for a 10% dropout rate, 15 participants per group are required. With 3 groups, the total sample size will therefore be 45 participants in total. Recruitment will take place across the 2 participating centers (Anoia and Bages), with approximately 7 to 8 participants per group expected to be recruited at each center.

The sample will be selected (1) by means of a medical history review by nursing or medical personnel; if the health professional considers that the patient meets the criteria, they will refer the patient to the research physiotherapist; and (2) indirectly, by putting up posters in *casals cívics* (civic facilities) and pharmacies in the city. Anyone learning about the study this way can make an appointment with their health professional of reference (ie, nursing or medical staff) and discuss their interest in participating in the study. If the health care professional confirms that the patient meets the criteria, they will refer the patient to the research physiotherapist.

The randomization and allocation of patients will be performed by simple randomization using the specialized software RStudio (version 4.2.1; R Foundation for Statistical Computing). The distribution is expected to be homogeneous between groups. Randomization will be conducted by an independent researcher, and allocation will be concealed using sequentially numbered, opaque, sealed envelopes prepared in advance. This procedure ensures allocation concealment and minimizes selection bias.

The chosen sample size is based on feasibility and resource availability and is sufficient to detect large effect sizes. This study aims to assess the feasibility and potential impact of the intervention and to provide effect size estimates to guide future large-scale trials.

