## Discussion

### Principal Anticipated Findings

We anticipate that the structured rehabilitation program combining behavioral reeducation and abdominal massage will lead to a reduction in chronic constipation symptoms and laxative use at 3 and 6 months after the intervention. We also expect improvements in quality of life, particularly among participants receiving both behavioral education and massage therapy. Furthermore, we expect that both intervention groups will show improvements compared to the control group, but that the BIM group will experience greater improvements.

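### The main variable has two co-equal time points and two control contrasts at 5%, but the sample size covers one contrast at 3 months, so the primary error rate exceeds 5% under most readings.

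*Protocol article*

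**What the plan says.** - **Main variable** (Statistical Analysis): "The main variable will be the percentage of patients with constipation 3 and 6 months after the start of treatment for each group". The two times stand side by side, and neither is called primary.
- **Test** (same section): "Prevalence will be estimated and analyzed using the" chi-square test. Whether this is one 3-group test or separate pairwise tests is not stated.
- **Contrasts** (same section): "the relative risk will be estimated to compare the reduction between the two intervention groups with respect to the control group". This gives BI versus control and BIM versus control.
- **Level** (same section): "Analyses will use 95% CIs, and the significance level will be set at 5" percent. No split or order accompanies it.
- **Objective and Progress**: the primary objective, at the end of the Introduction, lists 3, 6 and 12 months and adds laxative use. The Progress section says the primary and secondary outcomes are assessed at all three times.
- **Sample size** (Sample and Randomization): the calculation assumes that "approximately 90% of patients in the control group would remain constipated at 3 months" and that "this proportion would decrease to 40% in the intervention groups (BI and BIM"). It uses 80% power, two-sided 5% and 10% dropout, and arrives at 15 per group. Only 3 months enters it.
- **Expectation** (Principal Anticipated Findings): both intervention groups improve on control, but "the BIM group will experience greater improvements".

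**The concern.** The article gives three different accounts of when the primary outcome is judged: 3 months in the sample size, 3 and 6 months in the analysis, and 3, 6 and 12 months in the objective. It also sets two intervention groups against control, while the power statement covers one comparison. An analyst who follows the text can report a primary success from either group at either time at a nominal 5%. That 5% is then not the error rate of the trial's main claim, and the stated 80% power does not belong to a procedure that controls the error across those comparisons.

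**Working it through.** **1. Reproducing the stated 15 per group.** Inputs from Sample and Randomization: p1 = 0.90, p2 = 0.40, two-sided alpha 0.05, power 0.80, dropout 10%. The mean rate is 0.65. The pooled normal formula for one contrast is

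n = [z(1−alpha/2)·√(2·0.65·0.35) + z(0.80)·√(0.90·0.10 + 0.40·0.60)]² / 0.50²

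= [1.960 × 0.6745 + 0.8416 × 0.5745]² / 0.25 = 1.8056² / 0.25 = 13.04.

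Dividing by 0.9 gives 14.5, so 15. Rounding to 14 before the dropout step gives 16. The arcsine formula gives 12.3, so 13, and 13/0.9 = 14.4, so 15. The stated size therefore fits one pairwise contrast, at one time, at the full 5%.

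**2. The same formula with a continuity correction.** n/4 × [1 + √(1 + 4/(n × 0.50))]² with n = 13.04 gives 3.26 × (1 + 1.270)² = 16.8, so 17 evaluable. Then 16.8/0.9 = 18.7, so 19 randomised. The stated 15 does not fit a continuity-corrected test.

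**3. Splitting alpha over the two control contrasts at 3 months (0.025 each).** n = [2.241 × 0.6745 + 0.4835]² / 0.25 = 15.93, so 16 evaluable. Then 15.93/0.9 = 17.7, so 18 randomised. With 15 randomised and 10% dropout, 15 × 0.9 = 13.5, so 13 to 14 are evaluable. Exact power of the uncorrected chi-square test at 0.025 is then 71.0% (13) and 77.1% (14).

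**4. False-positive chance under no effect.** As a rough guide, four independent tests give 1 − 0.95⁴ = 18.5%. The real tests share a control group and the same patients, so the error was simulated: 15 per arm, the same true rate in all arms and at both times, latent within-person correlation of 0.5 to 0.9 between 3 and 6 months, and success on any test counted. The common rate, the correlation and the chi-square variant are assumptions. The only rate the article offers for patients without an effective intervention is about 90%. The 65% row value is the midpoint of 90% and 40%.

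| Reading of the plan | Common rate 90% | Lower common rate |
|---|---|---|
| One 3-group chi-square test at each of 3 and 6 months | about 6% to 7% | about 8% to 10% (rate 50% to 75%) |
| Two control contrasts at both times, uncorrected | about 8% to 9% | about 15% to 18% (rate 65% to 75%) |
| Two control contrasts at both times, continuity-corrected | about 0.4% | about 4.5% to 6% (rate 50% to 75%) |

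Tests at 12 months are not in these figures and could only raise them. With 13 per arm and correlation 0 to 0.7, the uncorrected four-test figures move to about 6% to 7% at a 90% rate and 18% to 22% at 65%.

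**5. BIM versus BI.** The sample size assumes 40% in both groups, so the design contains no difference between them to detect. With 15 per arm at 40% each, the 95% CI half-width for the difference is 1.96 × √(2 × 0.40 × 0.60 / 15) = 0.35, about 35 percentage points either way.

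**The case against.** Four points can fairly be made.

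- **Pairwise tests are not written for the main variable.** The section names a chi-square test without saying how many, and it sets the intervention groups against control by relative risk, which is estimation. Pairwise tests are named only for the continuous secondary variable. This stands. It is why the 3-group reading, at about 6% to 10%, must be reported beside the pairwise one.
- **The size depends on assumed inputs.** This stands too. At the article's own 90% rate the four-test error is 8% to 9%, and a continuity correction brings it far below 5% there and close to 5% at lower rates. But the stated 15 per group does not fit a corrected test.
- **The article also states a feasibility aim.** It wants effect size estimates for later trials and concedes that the sample is small. This lowers the weight of the point. It does not remove it, because the same section makes an 80% power claim at 5% and the Conclusions promise evidence of efficacy.
- **Multiplicity procedures are commonly left to the analysis plan, which is not shown.** True of the procedure. The conflict over which times are primary is in the article itself, and no analysis plan can agree with all three statements.

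A reader might go further, count BIM versus BI as a third contrast, and conclude that the trial's error rate is above 20%. The documents do not support that. The comparison is an expectation in the Discussion, not a planned test of the main variable. Nor does that expectation need rewriting, since a hypothesis is not a planned claim.

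**Conclusion.** The point holds in a bounded form. The article fixes no single primary time or contrast for the main variable, while its sample size covers one contrast at 3 months. If any success counts as primary, the error under no effect is above 5% on every uncorrected reading: about 6% to 10% with a 3-group test at each of two times, and from 8% to 9% (common rate 90%) up to 15% to 18% (65% to 75%) with two control contrasts at two times. These figures rest on 15 per arm, an uncorrected chi-square test and latent correlation 0.5 to 0.9. A reader might take the upper figure as a fixed property of the trial. It is not, because it requires separate pairwise tests and a common rate well below the one the article assumes for control. Simple alpha splitting would bring power for each contrast to about 71% to 77% with 13 to 14 evaluable per arm. This should be fixed before analysis. Given the stated feasibility aim, it is not a fatal defect.

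**What to change.** In Statistical Analysis, name 3 months, the time used for the sample size, as the single primary time point. Align the primary objective and the Progress section, with 6 and 12 months as secondary.

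State one prespecified procedure for the two control contrasts at 3 months that keeps the full 5% at the first step. Either of these serves:

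- a 3-group chi-square test as a gate, followed by the two pairwise contrasts, each at 5%. This controls the error because both contrasts can be null together only when all three groups are equal, which is what the gate tests;
- a fixed order, for example BIM versus control and then BI versus control, each at 5%. This order is one valid choice among several.

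State which chi-square variant is used. Report BIM versus BI on the main variable as an estimate with a 95% CI, without a confirmatory claim.

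The cost is wording, settled before the data are analysed, with no extra patients. In a fixed order the first contrast keeps the power it was sized for. With a gate, the first step is a different test from the one in the sample size calculation, so its power should be checked. In both cases later comparisons can be claimed only if the earlier step succeeds, and the 6- and 12-month results become supportive.
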